## 1. INTRODUCTION AND RATIONALE

A cholesteatoma manifests through the retraction or ingrowth of the tympanic membrane's skin into the middle ear, thereby inducing chronic inflammation of the middle ear. It is diagnosed in the Netherlands approximately 1600 times per year. Due to the chronic nature of a cholesteatoma, this patient group presents frequently to the ENT outpatient clinic over a long period of time. Consequences of this pathology arise from the erosion and inflammation of surrounding structures resulting in a constellation of symptoms such as hearing loss, ear drainage and/or the presence of unresponsive granulation tissue. Additionally, patients may experience vertigo, tinnitus, earache, a feeling of pressure on/in the ear, change in taste, and an itch. These problems can have a severe impact, not only on physical health but are also associated with a negative effect on psychosocial wellbeing and the quality of life. The only effective treatment is the surgical removal of cholesteatoma. In the absence of surgical intervention, it can lead to severe complications, including meningitis, brain abscess, facial nerve paralysis, or permanent loss of auditory or vestibular function.

The goal of cholesteatoma treatment is to eradicate the disease and create a safe and dry ear, while preventing recurrence of pathology and preserving, or even optimizing, hearing. The best surgical approach has been subject of debate for decades. The two traditional approaches are: canal wall down (CWD) and canal wall up (CWU) tympanomastoidectomy. Although they both have their advantages and disadvantages, the CWU technique has increasingly become the standard approach. CWD surgery results in a radical cavity, which gives a wide visual exposure of the disease for removal and therefore minimizes the chance of leaving cholesteatoma behind. However, a radical cavity creates a situation that requires regular debridement, increased risk of recurrent infections, and makes the fitting of hearing aids more challenging. The CWU approach on the contrary, maintains the normal anatomy of the bony part of the ear canal. It results in less frequent inflammations, hearing aids fit better and the regular outpatient cleaning of the ear is not indicated (1,2). However, the major issue with the CWU treatment is the higher odds of recurrent and residual disease. Whereas CWD tympanomastoidectomy show recidivism - including both recurrent and residual disease - rates of 0 to 17%, CWU tympanomastoidectomy rates vary between 9% and 70% (3,4).

Over the past decade, there has been growing interest in finding ways to decrease the disease recurrence rates and improve post-operative hearing outcomes. One promising technique is the obliteration of the mastoid and epitympanic area after either CWD or CWU tympanomastoidectomy. Obliteration is the act of filling the cavity that is created to reach the middle ear with either bone dust (sometimes also referred to as bone pâté) or artificial material. The purpose is to create a situation in which the obliteration material prevents the tympanic membrane from retracting and therefore lowers the chance of cholesteatoma recurrence. Mercke was one of the first otologic surgeons to present promising outcomes after obliteration in combination with CWD tympanomastoidectomy (5).

When Mercke first presented his results, the so called 'diffusion weighted magnetic resonance imaging' (DW-MRI) was not yet developed, making the detection of cholesteatoma during follow-up more difficult. At this time, patients traditionally underwent a 'second-look' operation, meaning that after a certain period the ear was surgically opened again to check if the disease had come back. Surgeons that are opposed to or do not utilize the obliteration technique may be afraid that it might be more challenging to detect and remove a cholesteatoma that might have been left behind after obliteration. "The main limitation of the technique is the inability to explore the mastoid cavity during follow-up with the risk of developing a "silent cholesteatoma", making radiological follow-up essential"(6). The development of the DW-MRI changed this somewhat by providing more diagnostic assurance and is currently used for the follow-up of patients that have been operated on. With the invention of the DW-MRI, the obliteration technique was therefore reintroduced and performed also subsequent to the CWU approach as patients could be followed more reliably and more otologists started believing in and using the obliteration technique. However, a limitation of radiological follow-up is the sensitivity of a DW-MRI, which ranges from 40-100% and the fact that cholesteatoma's are only detected when they are larger than 3mm in size (7–16).

Recently, van der Toom et al. showed in their systematic review that mastoid obliteration seems to reduce recurrence rates for both the CWD and CWU approach when compared to CWD and CWU without obliteration (17). While they found recurrent and residual disease rates of 5.9% and 5.8%, respectively, for the CWD technique, the outcomes for CWU tympanomastoidectomy were better. For the latter technique, they presented a recurrent disease rate of 0.28% and a residual disease rate of 4.2%. Combining the CWU tympanomastoidectomy and obliteration technique therefore seems a good solution to preserve the normal anatomy of the ear canal, as well as minimize the chance of contracting recurrent or residual cholesteatoma.

Whether surgeons do or do not obliterate the mastoid cavity after CWU tympanomastoidectomy today, seems to depend mostly on their personal experience, preferences, and scientific beliefs. Within the present ENT community, the usefulness of the obliteration is still widely discussed and is still a topic of current interest in literature, during congresses and within ENT-societies. The superiority of the technique is merely explored retrospectively in the literature with several confounding factors and a high risk of bias (such as difference in but not limited to; patient-related factors, surgical technique; obliteration material; follow-up periods; exclusion/inclusion criteria). Furthermore, current research rarely categorizes outcomes based on cholesteatoma extension and localisation, as for example classified using the STAMCO stages (18).

In addition to recidivism of cholesteatoma, hearing is another important outcome measure. In the literature, most research is conducted on hearing outcomes after CWD or canal wall reconstruction surgery with mastoid and epitympanic obliteration. Numerous studies show that these two similar techniques preserve preoperative hearing outcomes, or even moderately improve it (19–23). However, there is limited literature available on hearing outcomes following CWU with obliteration. The few retrospective studies that have recently been carried out show promising results that this approach also ensures hearing preservation (24–26). When using the obliteration technique in the epitympanum (a part of the middle ear), a part of the ossicular chain (part of the malleus and incus) must be removed, which poses a risk for hearing loss after surgery. It is therefore useful to investigate the relation between CWU tympanomastoidectomy with obliteration and hearing outcomes to either confirm or deny the retrospective evidence that recurrence and residual rates are lower due to the obliteration.

Since the preferred technique of the otologic surgeon is merely supported by retrospective data, the need for high quality data to provide an answer to this debate is clear. Bringing change into practice is a difficult task that must be supported by high quality prospective research. The aim of this randomized controlled trial is therefore, firstly, to determine whether CWU tympanomastoidectomy with obliteration reduces the recurrence and residual rates of cholesteatoma compared to CWU tympanomastoidectomy without obliteration. Secondly, hearing outcomes will be evaluated to investigate whether one of the two mentioned techniques result in better post-operative hearing. Thirdly, the quality of life will be measured using a validated questionnaire (OQUA) and the cost-efficiency will be calculated.

## 2. OBJECTIVES

**Primary Objective:** The primary aim of this randomized controlled trial is to determine whether CWU tympanomastoidectomy with obliteration reduces the recurrence and residual rates of cholesteatoma compared to CWU tympanomastoidectomy without obliteration.

**Secondary Objective(s):**

- Hearing outcomes
- Health-related quality of life
- Describing localization and disease extension using the STAMCO classification
- Health economic cost analysis
- Comparing any differences in patient and surgical characteristics

## 3. STUDY DESIGN

The proposed study design is a multicenter two-armed randomized controlled trial. It will be conducted using a single blind method. The patients will not know which surgical approach they received, which is necessary for the subjective measurement of the quality of life questionnaire. The surgeon will know which procedure he/she has performed as this is unavoidable. The surgeon will not write down which procedure the patient received in the surgical report or in the letter to the general practitioner. It will only be recorded in Castor and in the RFS map. De blinding (single-sided) will only be lifted if it is in the interest of the safety of the participant. De participant and/or general practitioner can request this from the treating physician (ENT-surgeon) who performed the surgery. The ENT-surgeon will decide if lifting of the blinding is necessary and inform the researcher about this event. In case of emergency and in absence of the treating physician, other medical specialists can lift the blinding by checking the placement of the patient in the RFS map. All medical specialists have access to the RFS map with information of the participants where an inclusion table with randomization is stored. This way it is possible to lift blinding 24 hours a day. After completion of the last quality of life questionnaire (at 36 months) the treatment group will also be added to the patient file in HiX. The patients are randomly assigned to one of the two groups (A or B). A web-based randomization tool in Castor will be used for the allocation and will be accessed by the researcher. The study will be conducted with a sufficient duration to gather the sample size needed. The setting is multi-center; both secondary and tertiary university hospitals will participate. The estimated duration of the study is 7 years (84 months): 1 year will be allocated for completing the inclusions and follow-up will be completed in the following 5 years. The last year will be used to analyze the data and round up the trial.

All pre-operative measurements are part of standard care in the Netherlands and Belgium. Pre-operatively patients receive an audiometric exam, a physical examination of the ear, a CT-scan and fill in the patient-reported outcome measure (PROM). Follow-up will be planned at least at 6-18 weeks, at around 1 year and at around 3 years after surgery. It is important to note that conducting a CT scan and audiometry preoperatively as well as the DW-MRI's after 1 and 3 years are part of the standard care. In line with standard care, if there is a suspicion for recurrent or residual pathology (either clinically by micro-otoscopy or radiologically by DW-MRI) the treating physician will perform a revision surgery. If during revision surgery the suspicion is confirmed, the type of recidivism (residual or recurrent) is recorded and the follow-up of the patient ends. Data that is collected up until the point of detection of residual or recurrent disease will be used for analysis (this is not an exclusion criterium). If the suspicion is not confirmed (false-positive) then the patient will continue the follow-up as planned (unless a reconstructive procedure with the goal of improving hearing has been performed). During the three years of follow-up, patients should not undergo another type of ear surgery. If this is unavoidable, as judged by the treating physicians, the patient will be retrospectively excluded. In order to ensure that the same surgical data is collected in all participating centers, a standardized operation report will be written and shared by the sponsor (UMC Utrecht). This operation report will be recorded in the electronic patient dossier (with the exception of the information if obliteration was used or not) and transferred to Castor EDC. In Castor there will be a variable to also record if obliteration has taken place or not. The only methodology that is different to standard care is the randomization of the patients and the completion of the questionnaire. It is important to note that the technique used for the obliteration technique differs slightly between centers. The exact surgical technique will be described by the participating otologists and included in the description of the study, for example in a publication.

**Figure 1.** Flowchart of the study. *Standard care is indicated by \**[figure not shown]

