## 6. METHODS

### 6.1 Study parameters/endpoints

#### 6.1.1 Main study parameter/endpoint

The main endpoint is the number of patients with recurrent or residual cholesteatoma. Follow-up for recurrent/residual cholesteatoma will be performed after 6-18 weeks and after approximately 1, 3 and 5 years. Follow-up is done by micro-otoscopy and DW-MRI scans (after 1, 3 and 5 years) (see figure 1 for the follow-up steps). A newly formed retraction pocket from the tympanic membrane correlates with recurrent disease (clinical diagnosis), whereas cholesteatoma formation behind a normal or an intact tympanic membrane after primary surgery correlates with residual disease (radiologic diagnosis).

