## 6.2 Randomisation, blinding and treatment allocation

If they sign the informed consent form they will be randomly allocated to one of the two treatment groups (A or B) using the Randomization Tool in Castor. Patients will be randomly assigned to one of the two study groups (A or B). A website randomisation program built within Castor will be used for the randomization. After informed consent, patients will be randomized. This is a single blind study, meaning that only participants are blinded for the treatment allocation. The surgeons cannot be blinded, as they will know which procedure they performed. The surgeon will not write down which procedure the patient received in the surgical report or in the letter to the general practitioner. It will only be recorded in Castor and in the RFS map. De blinding (single-sided) will only be lifted if it is in the interest of the safety of the participant. De participant and/or general practitioner can request this from the treating physician (ENT-surgeon) who performed the surgery. The ENT-surgeon will decide if lifting of the blinding is necessary and inform the researcher about this event. Only in case of medical emergency and in absence of the treating physician, other medical specialists can lift the blinding by checking the placement of the patient in the RFS map. All medical specialists have access to the RFS map with information of the participants where an inclusion table with randomization is stored. This way it is possible to lift blinding 24 hours a day.

Stratification will be used to distribute the two groups as evenly as possible between the participating centres. Patients are randomized into one of two groups in an equal 1:1 allocation ratio. A 4,6,8 block randomization will be used.

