**Table 1. Study procedures**

| Measurement                                                                                               | Pre-operative (baseline) | Surgery Day 0 | Follow-up (post-operative) |                         |                         |                         |
|-----------------------------------------------------------------------------------------------------------|--------------------------|---------------|----------------------------|-------------------------|-------------------------|-------------------------|
|                                                                                                           |                          |               | 6-18 weeks                 | 12 months (+/- 1 month) | 36 months (+/- 1 month) | 60 months (+/- 1 month) |
| CT-scan                                                                                                   | X*                       |               |                            | (X)*                    | (X)*                    | (X)*                    |
| Audiometry                                                                                                | X*                       |               | X*                         | X*                      |                         |                         |
| Visit outpatient clinic and micro-otoscopy                                                                | X*                       |               | X*                         | X*                      | X*                      | X*                      |
| Inclusion                                                                                                 | X                        |               |                            |                         |                         |                         |
| Randomization                                                                                             | X                        |               |                            |                         |                         |                         |
| Surgery                                                                                                   |                          | X*            |                            |                         |                         |                         |

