### **8.1 Primary study parameter(s)**

The data of our primary outcome are quantitative and will be presented as frequencies and proportions. To compare the difference in recidivism (recurrent and residual disease) at 12, 36 and 60 months between both surgical groups the Chi-squared test or Fisher's exact test will be used. The relative risk (RR) and absolute risk difference (RD) will be calculated as effect sizes using a generalized linear model for binomial outcome with a log-link (for RR) and identity link (RD). The primary analysis will be adjusted for site by including centre as covariate in a logistic regression model with treatment arm as the main predictor. All effect sizes will be accompanied by 95% confidence intervals. To graphically demonstrate the rates of recidivism, recurrent and residual disease over the follow-up time, a Kaplan-Meier analysis will also be performed and survival curves will be constructed. Multiple imputation will be used to deal with missing

outcomes. A 20% difference is defined as the threshold for clinical relevance and will be consistently applied in both clinical effectiveness analyses and the health economic evaluation.

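### Allocation enters the patient file at 36 months, so participant blinding and file concealment lapse 24 months before the last primary-endpoint assessment

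*Protocol*

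**What the plan says.** **When the arm is disclosed.** Section 3 withholds the procedure from the operation report and the letter to the general practitioner, and confines the record of allocation to Castor and the RFS map. It permits unblinding only for the participant's safety. It then adds that, after the final quality-of-life questionnaire, "at 36 months) the treatment group will also be added to the patient file in HiX".

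**When the primary endpoint is assessed.** Section 6.1.1: "Follow-up is done by micro-otoscopy and DW-MRI scans (after 1, 3 and 5 years"). Table 1 has a final visit at "60 months (+/- 1 month") with DW-MRI, micro-otoscopy and registration of recurrent or residual disease. Section 8.1 compares recidivism "at 12, 36 and 60 months between both surgical groups".

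**Who is blinded, and why.** Section 6.2: "This is a single blind study, meaning that only participants are blinded for the treatment allocation". Section 3 gives the purpose as one "which is necessary for the subjective measurement of the quality of life questionnaire". On access, Section 3 states: "All medical specialists have access to the RFS map with information of the participants where an inclusion table with randomization is stored".

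**What Section 6.2 omits.** It repeats the rules on where allocation is recorded and when blinding may be lifted, but not the 36-month file entry.

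**The concern.** The disclosure is tied to the last measurement of a secondary outcome. The primary endpoint has one more scheduled assessment, and the protocol gives no reason for disclosing before it.

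Three things at 60 months could come to depend on arm: whether the patient attends, which symptoms the patient reports, and how readily a clinician using the file suspects disease. Suspicion matters because, under Section 3, it leads to the revision surgery at which an event is confirmed. The suspicion step leaves room for judgement. Section 1 gives DW-MRI sensitivity as 40-100%, says the use of obliteration depends mostly on surgeons' experience and beliefs, and reports a fear that obliteration hides disease left behind. Section 8.2 itself treats differential attrition as something to account for.

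There is also a plain inconsistency. A routine file entry at 36 months is neither in Castor nor in the RFS map, and it is not prompted by safety.

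**Working it through.** **1. The plan's own design figures.** Inputs from Section 4.4: 0.20 versus 0.40, two-sided alpha 0.05, pooled Z test, 80 per arm, 10% dropout. Exact binomial enumeration of that test at 80 per arm gives power 0.8009 and actual alpha 0.0472 (both arms at 0.40), as printed in the table. Dropout: 160 / 0.90 = 177.8, rounded up to 178. The design reproduces, and nothing below changes it.

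**2. The gap.** Last primary assessment at 60 months (Table 1, Section 8.1) minus file entry at 36 months (Section 3) = 24 months.

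**3. Which errors can move the primary result.** Under Section 3, a suspicion not confirmed at revision surgery is a false positive and the patient normally continues follow-up. A false call therefore creates no event. Bias comes mainly from true disease, first detectable at 60 months, that is missed or not attended for more often in one arm.

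**4. Size with no true effect.** Let p be the cumulative event rate at 60 months, s the share of events first found at 60 months, and m the fraction of those missed in one arm only.

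Spurious difference = p x s x m

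The range of p, 0.20 to 0.40, spans the planning rates. The documents give neither s nor m; both are assumed to lie between 0.10 and 0.30.

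- Smallest: 0.20 x 0.10 x 0.10 = 0.002, or 0.2 points.
- Largest: 0.40 x 0.30 x 0.30 = 0.036, or 3.6 points.

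Over this grid the exact two-sided rejection rate at 80 per arm runs from 0.048 to 0.073. With no differential detection it is 0.047 to 0.051 for the same p.

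**5. Size with the planned effect (0.20 versus 0.40), largest assumed loss (s = m = 0.30).**

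- Disease missed in the non-obliteration arm: 0.40 x (1 - 0.09) - 0.20 = 0.164, power 0.65.
- Disease missed in the obliteration arm: 0.40 - 0.20 x (1 - 0.09) = 0.218, power 0.87.

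For scale, one patient in an arm of 80 is 1/80 = 1.25 points.

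**6. Sections 3 and 6.2 side by side.** Both state the two restrictive rules; only Section 3 carries the 36-month entry. Someone working from Section 6.2 would conclude that the arm never reaches the patient file. Section 3 also speaks of three years of follow-up when it restricts other ear surgery. The 36-month trigger may therefore predate the 60-month visit, but that is an inference.

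**The case against.** The strongest counter-argument is that the timing matches the stated purpose. Participants are blinded for the questionnaires, and the last of these is at 36 months. The primary endpoint rests on imaging and otoscopy, with confirmation at surgery. On that view a longer blind is a preference. This has some force and keeps the point modest. It does not explain why concealment that already exists should end before the last primary assessment, and it leaves Sections 3 and 6.2 unreconciled.

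A reader might infer that the file entry unblinds the reading of the 60-month scans. The documents do not support that. No radiologist or outcome assessor is blinded at 12, 36 or 60 months, the operating surgeon knows the arm, and all medical specialists can reach the allocation table throughout. Nor do the documents say whether imaging itself shows the obliteration. What is lost is practical concealment: an arm shown in the routine file is easier to see than one held in a separate map.

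A reader might also infer that patients are told their arm at 36 months. Section 3 says only that it goes into the file; that they learn it is plausible but not stated.

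Finally, one might apply an assumed 5-point difference in calling or missing disease to everyone still event-free (60% and 80% at the planning rates) and obtain 0.05 x 0.60 = 3 to 0.05 x 0.80 = 4 points. That overstates the exposure. It counts false calls, which surgery would not confirm, and covers patients with no disease to miss.

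**Conclusion.** The point holds in a limited form. The 36-month entry leaves the participant blind and the file concealment unprotected for the final 24 months of primary-endpoint follow-up. The only apparent reason is the timing of the last questionnaire, and Section 6.2 does not carry the exception.

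Any resulting bias is limited to disease first detectable at 60 months. On the assumed inputs it is about 0.2 to 3.6 percentage points with no true effect, against a planned difference of 20 points, and its direction is unknown. That range depends wholly on the assumed share of events first found at 60 months and the assumed differential loss. The documents supply neither, and they do not show that such a loss will occur. This is an inexpensive safeguard and a consistency correction; it does not invalidate the primary analysis.

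**What to change.** Change the sentence in Section 3 so that the treatment group is added to the patient file only after that patient's 60-month DW-MRI and micro-otoscopy results are recorded, or after confirmed recidivism, when follow-up ends anyway. The sentence also needs a default for patients who miss the 60-month visit. Bring Section 6.2 into line, so that both sections agree on where allocation is recorded and when blinding ends. Emergency unblinding stays as written.

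**Cost.** The file shows the arm up to two years later. The sample size stays at 178 and no procedure is added. Inclusion runs from February 2025 (Section 4.1) and the protocol version is dated 25-03-2026, so the first 36-month entries fall in about early 2028 and the change can still precede them.

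**Limit.** The change does not by itself blind scan reading; it only extends existing concealment to the last primary assessment.

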**Main study parameters/endpoints:** Rates of recurrent or residual cholesteatoma are evaluated by diffusion-weighted magnetic resonance imaging (DW-MRI) and micro-otoscopy after approximately one, three and five years. If diffusion restriction is seen on DW-MRI and/or retraction of the tympanic membrane is seen during micro-otoscopy, suspicion for recurrent or residual disease will be recorded. To confirm the diagnosis and to determine whether the cholesteatoma is either recurrent or residual, we will analyse the tympanic membrane description at the beginning of the revision surgery. All other surgical outcome measures are recorded in the surgical report. Pure tone audiograms, including air and bone conduction, and speech recognition scores are evaluated pre- and postoperatively for each patient. The EQ-5D-5L, HUI-3, iMCQ and iPCQ questionnaires will be filled in once pre- and a two times postoperatively by every patient. The OQUA will be filled in once preoperatively and three times postoperatively. The direct health-care costs will be recorded for the sponsor centre and extrapolated for the whole trial.

**Nature and extent of the burden and risks associated with participation, benefit and group relatedness:** The burden patients will experience by participating in this study will be filling in the questionnaire multiple times. The surgery, along with the imaging procedures (CT and DW-MRI), audiometry and follow-up appointments, is part of standard care and takes place irrespective of participation in this study.

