Quality of life related to the procedures and (longer-term) hearing loss will be collected with HUI-3, specific for hearing problems. To validate use of HUI-3 in a cost-utility analyses, the EQ-5D-5L will be collected as well. Costs and quality of life will be calculated for each patient and for each health state in the decision-analytical model. Extensive sensitivity analyses will be performed, including deterministic (DSA), probabilistic sensitivity analysis (PSA), scenario analyses and VOI analyses, to estimate the impact of uncertainty on cost-effectiveness. The results of the cost effectiveness analysis will be combined with observed number eligible patients to estimate the budget impact.

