### PROM (OQUA)

- The OQUA is a validated otological questionnaire and includes 34 questions, covering eight major types of ear complaints (earache, pressure in the ear, hearing loss, tinnitus, otorrhoea, itch, dizziness, and loss of taste). It measures the frequency and severity of these ear complaints and the impact on quality of life. The frequency of the ear complaints is expressed on a scale from 1-5, whereas the impact on quality of life is answered on a scale from 0-100. OQUA will be compared between treatment arms using a mixed model for repeated measures (MMRM) with fixed effects for treatment arm and timepoint (12 months, 36 months) and their two-way interaction. Analyses will be adjusted for OQUA at baseline. Primary inference will be based on the estimated mean difference at 36 months.

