## **Economic evaluation**

- A cost utility analysis will be performed as described under the methods section.

The amount of missing data will be mentioned in the results. Missing data will be imputed using multiple imputation. All analyses will be performed on an intention-to-treat basis.

Additionally, dropout rates will be monitored, and any differential attrition between treatment arms will be appropriately accounted for in the statistical analysis.

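### Follow-up ends at confirmed recidivism, so almost no patient-reported quality of life, utility, resource-use or productivity data are collected after it

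*Protocol*

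**What the plan says.** Protocol Section 3 (Study design) states that when revision surgery confirms the suspicion, "the type of recidivism (residual or recurrent) is recorded and the follow-up of the patient ends". It adds: "Data that is collected up until the point of detection of residual or recurrent disease will be used for analysis". By contrast, "If the suspicion is not confirmed (false-positive) then the patient will continue the follow-up as planned", except where a hearing reconstruction was done. The stop is therefore triggered by the primary outcome itself.

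Other sections count on data from everyone:

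- **Summary:** "The EQ-5D-5L, HUI-3, iMCQ and iPCQ questionnaires will be filled in once pre- and a two times postoperatively by every patient". Table 1 (Section 6.3) places these forms at 12 and 36 months and the postoperative OQUA at 6-18 weeks, 12 and 36 months. No questionnaire is scheduled at 60 months.
- **Section 8.2, PROM (OQUA):** "Primary inference will be based on the estimated mean difference at 36 months".
- **Section 6.1.2, economic evaluation:** "Costs and quality of life will be calculated for each patient and for each health state in the decision-analytical model".
- **End of Section 8.2:** "Missing data will be imputed using multiple imputation", all analyses are by intention to treat, and differential attrition is to be accounted for, with no method named.

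**The concern.** The patients who stop giving data are those whose surgery failed, and under the trial's own hypothesis there are more of them in the arm without obliteration. Fewer recidivisms, and less of the burden that follows, is one obvious way in which obliteration could improve quality of life and save costs. If 36-month values are missing because recidivism occurred, and are filled in largely from patients in whom it did not, that benefit tends to be understated. The lifetime model also needs a utility and a patient-reported resource-use value for the state after recidivism, and the trial would hardly observe that state. An analysis plan can choose an imputation model, but it cannot recover forms that were never sent.

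**Working it through.** **1. The plan's own figure.** Inputs from Section 4.4: proportions 0.20 and 0.40, pooled Z test, two-sided alpha 0.05, 80 per arm. Exact binomial enumeration gives power 0.8009 and actual alpha 0.0472 (at a common proportion of 0.40), as printed. Dropout: 160 / (1 - 0.10) = 177.8, rounded up to 178, or 89 per arm. The sample size reproduces and is not in dispute. The two rates serve below as planning values.

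**2. Who loses which form.** Setting Section 3 against Table 1:

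| Recidivism confirmed | Questionnaires lost | Month-12 audiogram |
|---|---|---|
| Before the 12-month visit | 12 and 36 months | Lost |
| Between the 12- and 36-month forms | 36 months | Kept |
| After the 36-month form, on suspicion raised at that visit | None | Kept |
| After the 60-month visit | None | Kept |

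In the first two rows the remaining forms are cancelled. In the last two, no later form is scheduled. In no row does a scheduled form follow confirmation, and this does not depend on any assumed rate.

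**3. Size of the loss at 36 months.** Let f be the share of recidivism confirmed before the 36-month form. The protocol does not give f. It is assumed to lie between 0.25 and 1 and to be equal in both arms. Ordinary dropout is ignored.

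- Control: 89 x 0.40 x f = 35.6f
- Obliteration: 89 x 0.20 x f = 17.8f
- Share of all patients: 53.4f / 178 = 0.30f

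| f | Control | Obliteration | Share of 178 |
|---|---|---|---|
| 0.25 | 8.9 | 4.5 | 7.5% |
| 0.50 | 17.8 | 8.9 | 15% |
| 0.75 | 26.7 | 13.4 | 22.5% |
| 1.00 | 35.6 | 17.8 | 30% |

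The ratio between arms is 0.40f / 0.20f = 2 at every f. The share exceeds 10% once 0.30f > 0.10, that is, once f is above one third.

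**4. Direction of the bias.** Suppose confirmed recidivism worsens a score by d points at 36 months. The patients affected by the stop then contribute (0.40 - 0.20) x f x d to the true difference between arms. If their imputed values looked exactly like those of recidivism-free patients, that whole amount would vanish. For an assumed d = 10 this is 0.20 x 0.25 x 10 = 0.5 points to 0.20 x 1 x 10 = 2.0 points. These are ceilings, since earlier scores will carry some information into the imputation. The protocol gives neither d nor f.

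**The case against.** Several points on the other side are sound and limit the concern.

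- **Detection at month 36.** Follow-up ends at surgical confirmation, not at suspicion. A patient first suspected at the 36-month visit can normally still complete that form. A reader might infer that every 36-month value comes from a patient without recidivism; the schedule does not support that.
- **Earlier scores.** A patient detected at the 12-month scan already has OQUA values at baseline, 6-18 weeks and 12 months, the last possibly with disease present. A reader might infer that the whole recidivism-related effect is lost; that would need earlier scores to carry no signal. They do, however, pre-date the revision and cannot show its consequences.
- **Costs.** Section 6.1.2 collects surgical-report data from revision surgeries during follow-up, costs reinterventions bottom-up, and allows claims linkage. It would be wrong to infer that the trial has no cost data on recidivism. None of these sources supplies utilities or productivity losses.
- **Revision cases at entry.** Section 4.1 admits some revision surgery, so some post-revision utilities will exist. But Section 4.3 excludes ears already obliterated, so these patients cannot stand in for revision after obliteration.
- **Intention to treat.** Section 3 says that recidivism is not a reason for exclusion, and Section 8.2 analyses by intention to treat with imputation. Calling the comparisons not intention-to-treat goes too far. What is missing is a stated handling of confirmed recidivism.
- **Unseen analysis plan.** Imputation details may be given there. That answers the modelling question but not the missing observations.

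One might also read the end of follow-up as ending only surveillance for recidivism, with questionnaires going on. The Summary's reference to every patient gives this some support, but Section 3 places its data cut-off at detection and no section says that questionnaires continue.

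**Conclusion.** The concern holds for patient-reported secondary and economic data. As written, the protocol collects almost no OQUA, utility, resource-use or productivity data after confirmed recidivism, although the OQUA inference and the economic model call for them. The expected design loss at 36 months is 7.5% to 30% of 178 patients, twice as high in the control arm. This rests on the planning rates of 40% v 20%, which Section 4.4 gives without a time point, and on an assumed f of 0.25 to 1, equal in both arms. The upper end is extreme, because scans at 36 and 60 months will detect part of the recidivism. The 2:1 ratio holds only if the trial's alternative is true; in that case the bias works against obliteration and does not create a false benefit.

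A reader might infer damage to the main result. There is none: the primary event is already recorded when follow-up stops. Audiometry is affected only for confirmations before month 12. Severity: should-fix.

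**What to change.** In Section 3, state that confirmed recidivism counts as reaching the primary endpoint, and that OQUA, EQ-5D-5L, HUI-3, iMCQ and iPCQ continue on the original schedule to month 36. Amend the sentence that limits analysed data to the time before detection so that it agrees. In Section 8.2, state that the OQUA, utility and cost analyses use all values regardless of recidivism, and that the imputation model includes recidivism status and date. With forms continued, the loss caused by the stopping rule falls to zero in both arms, leaving only ordinary non-response.

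The cost is revised wording in the protocol and information letter and a few more forms for these patients. The questionnaires already run in Castor (Section 6.3), the OQUA link is e-mailed automatically (Section 10.1), and patients who leave the study stay in regular care (Section 6.6). The change concerns data collection only, not clinical management. It must be made while patients are still in follow-up, because these answers cannot be obtained later.
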